### Objectives

The objectives of the trial are to establish whether (1) new residents in Chinese older adult centers have higher PWB scores, happiness, and relaxation, as well as lower levels of loneliness and salivary cortisol, after engaging in Chinese art activities; (2) new residents in Chinese older adult centers have higher PWB scores, happiness, and relaxation, as well as lower levels of loneliness and salivary cortisol, after engaging in Chinese art activities and peer group participation; (3) new residents in Chinese older adult centers engaging in a Chinese art activity and peer group participation intervention have higher PWB scores, happiness, and relaxation, as well as lower levels of loneliness and salivary cortisol, than those who only engage in Chinese art activities; and (4) salivary cortisol can serve as a biomarker reflecting changes in PWB and relaxation.

On the basis of aesthetic theory and social support theory, we propose the following hypotheses: (1) for objectives 1 and 2, we hypothesize that both Chinese art activities and Chinese art activities with peer group participation will promote PWB, happiness, and relaxation and alleviate loneliness; (2) for objective 3, we hypothesize that peer group participation will have a stronger effect than Chinese art activities; and (3) for objective 4, we hypothesize that salivary cortisol will be a biological indicator of PWB and relaxation.

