### Trial Design

This multicenter randomized, assessor-blinded trial is structured according to the “max-min-con” principle [45,46]: maximizing experimental variance by ensuring that art activities and art activities with peer group participation are delivered consistently and distinctly from the control condition; minimizing error variance by using standardized protocols for art activities and art activities with peer group participation, trained research assistants (RAs), and reliable measurement instruments; and controlling extraneous variance through minimized randomization and blinding of outcome assessors.

This study has 3 intervention groups: group A (Chinese art activities), group B (Chinese art activities+peer group participation), and group C (regular care), with participants randomized at a 1:1:1 allocation ratio. The study will be conducted consecutively at 3 older adult centers. These 3 centers all belong to Suzhou Health and Elderly Care Industry Development Group Co, Ltd. After on-site inspection, it was determined that the inclusion criteria (affiliation, bed capacity, facilities, management support, and accessibility) were met to ensure feasibility and reasonable representativeness. Each center is treated as a randomization unit. Figure 2 delineates the implementation phase and the data collection procedures in the study. The intervention takes place over 3 sessions in a single week (Monday, Wednesday, and Friday). Baseline evaluations of PWB, loneliness, happiness, relaxation, and salivary cortisol levels are conducted before randomization.

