For the testing of objectives 1 and 2, a dual test of intra- and intergroup comparisons will be used. If the data are normally distributed, 2-tailed paired-sample *t* tests will be used for intragroup comparison of the Chinese art activities group or the Chinese art activities and peer group participation group. This will test the intervention effects of the Chinese art activities or Chinese art activities with peer group participation interventions on happiness, relaxation, loneliness, and salivary cortisol levels before and after the intervention (3 times). We will use independent-sample *t* tests to compare the effects of the Chinese art activities or Chinese art activities with peer group participation interventions on happiness, relaxation, loneliness, and salivary cortisol levels with the control group. For the testing of objective 3, an independent-sample *t* test will be used to compare the effects of the Chinese art activities with peer group participation and the Chinese art activities interventions on happiness, relaxation, loneliness, and salivary cortisol levels. For the testing of objective 4, salivary cortisol levels will be the main independent variable, and changes in PWB or relaxation will be divided into 3 quartiles as dependent variables. Ordered logistic regression analysis will be used to explore the association between salivary cortisol and these 2 variables. There will be no additional analyses.

Due to the harmless and short-term nature of this study, there will be very little missing data. Preliminary analysis will be conducted based on the complete case. We will use mean imputation for any missing data within a scale. Following the intention-to-treat principle, participants with intervention data will be included in the analysis.

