## Discussion

### Anticipated Findings

To our knowledge, this is the first exploratory study on the improvement effect of traditional Chinese art activities on PWB among individuals who are new residents of older adult centers. On the basis of our pilot study demonstrating the feasibility and potential of Chinese art activities and Chinese art activities with peer group participation, this multicenter RCT aims to provide preliminary evidence on the effectiveness of these interventions in institutional environments. By comparing the outcomes of both interventions, we expect to determine the best program that is suitable for individuals who are new residents of older adult centers. At the same time, we speculate that combining subjective scales with the objective indicator of salivary cortisol can effectively verify the positive effects of Chinese art activities and Chinese art activities with peer group participation and salivary cortisol will significantly correlate with the subjective results of PWB, which will further confirm the physiological basis for the effects of these interventions.

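### Objective 4 bands a continuous change into a self-contradictory three quartiles and leaves the cortisol predictor undefined, so cortisol change is not clearly tested against change in PWB or relaxation

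*Protocol article*

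**What the plan says.** The Objectives section asks, as its fourth aim, whether "salivary cortisol can serve as a biomarker reflecting changes in PWB and relaxation". The Statistical Methods section sets the analysis: "salivary cortisol levels will be the main independent variable, and changes in PWB or relaxation will be divided into 3 quartiles as dependent variables". It continues: "Ordered logistic regression analysis will be used to explore the association between salivary cortisol and these 2 variables", and closes the paragraph with "There will be no additional analyses".

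Table 1 of the Protocol article ticks salivary cortisol before and after each of three sessions (T1 to T3) and once at T4. The Trial Design section adds an earlier sample: "Baseline evaluations of PWB, loneliness, happiness, relaxation, and salivary cortisol levels are conducted before randomization". Table 1 has no cortisol tick at enrollment (T-1). PWB is ticked only at T-1 and T4.

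The Anticipated Findings section expects that "salivary cortisol will significantly correlate with the subjective results of PWB", and the Abstract's conclusions present the trial as an evaluation of cortisol as a biomarker for PWB.

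**The concern.** There are three difficulties, in descending order of firmness.

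1. **The outcome rule contradicts itself.** Quartiles have three cut points and give four groups; three groups are tertiles. Whether the ordinal outcome has three or four levels could be settled after the data are seen. Either version discards information from a continuous change score.
2. **The predictor is not tied to the objective.** The objective is about changes. Change appears explicitly only on the outcome side; the predictor is called a level, with no time point. The choice of sample affects both the strength and the sign of the association.
3. **No arm term is named.** The trial expects that "both Chinese art activities and Chinese art activities with peer group participation will promote PWB, happiness, and relaxation and alleviate loneliness", and objectives 1 and 2 also look for lower cortisol. If arm moves both variables and is left out of the model, they can be associated across the whole sample with no link between them within an arm.

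At stake is one of the trial's four objectives and the physiological interpretation that the discussion hopes to draw from it.

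**Working it through.** The plan gives no effect size, power or sample size for objective 4, so there is no stated figure to reproduce.

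**Inputs from the Protocol article.** 90 participants in three arms of 30; cortisol schedule as in Table 1 and Trial Design; a planning effect of d=0.92 (Sample Size, for loneliness), borrowed here only as a large arm effect.

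**Assumed inputs (not in the document).** Equal pre and post cortisol variances; pre-post correlation ρ of 0.4 to 0.8; true change-on-change correlation 0.3 or 0.4; outcome change related to cortisol only through cortisol change; arm effects of 0.5 or 0.92 SD on both variables in both active arms; two-sided α of 0.05.

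**Step 1: group sizes.** Three groups: 90/3 = 30 each. Four groups: 90/4 = 22.5, so 22 or 23 each.

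**Step 2: number of cortisol samples.** 3 sessions × 2 + 1 at T4 = 7 by Table 1, or 8 with the baseline sample in Trial Design.

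**Step 3: level as proxy for change.** With common variance σ², Var(post − pre) = 2σ²(1 − ρ) and Cov(post, post − pre) = σ²(1 − ρ). Hence

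corr(post, change) = √((1 − ρ)/2) and corr(pre, change) = −√((1 − ρ)/2).

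At ρ = 0.6 this is √0.2 = 0.447, so +0.447 for the post level and −0.447 for the pre level.

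**Step 4: power at n=90.** The test is Fisher's z, with atanh(r) × √87 compared with 1.96.

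| Predictor | ρ | Correlation with outcome change (absolute) | Power |
|---|---|---|---|
| Cortisol change | any | 0.30 | 82% |
| Single level | 0.4 | 0.30 × 0.548 = 0.164 | 34% |
| Single level | 0.6 | 0.30 × 0.447 = 0.134 | 24% |
| Single level | 0.8 | 0.30 × 0.316 = 0.095 | 14% |

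**Step 5: simulation of the ordinal model.** 3 × 30 participants, outcome in three groups, 250 replicates per scenario. With a true change-on-change correlation of 0.4 and no arm effect:

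| Predictor | Power, ρ = 0.5 | Power, ρ = 0.7 |
|---|---|---|
| Post level, no arm term | 42% | 28% |
| Pre level, no arm term | 40% | 26% |
| Cortisol change, with arm | 94% | 94% |

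**Step 6: cost of banding alone.** At a correlation of 0.3, three equal bands lower power from 83% to 73%. At 0.4, with arm in the model, the fall is from 98-99% to 94%.

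**Step 7: leaving arm out.** Share of simulated trials with a significant association when there is none within arms (range over ρ = 0.5 and 0.7):

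| Model | Arm effect 0.5 SD | Arm effect 0.92 SD |
|---|---|---|
| Post level, no arm term | 8% | 20-26% |
| Cortisol change, no arm term | 7% | 27% |
| Pre level, no arm term | 5% | 6% |
| Cortisol change, with arm | 6% | 6-7% |

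With 250 replicates the Monte Carlo standard error at 5% is √(0.05 × 0.95/250) = 1.4 points. The 7-8% at 0.5 SD is therefore only one to two standard errors above nominal.

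**The case against.** The best defence is that the text is loose rather than wrong. The phrase used for the predictor is the article's standing name for the cortisol variable, and the same section uses it for paired before-and-after tests, which are tests of change. A reader might infer that the plan chose a level over a change. The document does not support that; the fair reading is that the predictor is undefined. This stands, and the power loss in Steps 3 to 5 applies only if a level is in fact used. The sign reversal further depends on which sample is picked.

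A reader might also infer that the arms are pooled without adjustment. That would be read from silence. Cortisol is called the main independent variable, which leaves room for others, and a covariate list may sit in an analysis plan not shown. The sentence ruling out additional analyses does not forbid covariates in this one. So the arm point is conditional, and its size is slight at moderate arm effects.

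Finally, the trial calls itself exploratory, and the cost of banding alone is modest. Both are true. Neither repairs a category rule that contradicts itself, nor tells the analyst which of seven or eight cortisol values to enter.

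**Conclusion.** The point holds in this form. The outcome rule is wrong as written, it bands a continuous score without need, and the predictor is not defined in a way that matches an objective about changes.

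If a single level is used, it correlates with cortisol change at about 0.45 in absolute value (ρ = 0.6), and power for a true correlation of 0.3 falls from about 82% to 24% (34% to 14% for ρ from 0.4 to 0.8). If arm is omitted, the false-association rate is about 7-8% at arm effects of 0.5 SD and 20-27% at 0.92 SD, for the post level or cortisol change. All these figures are illustrative, because the correlations and arm effects are assumed. They take all 90 participants as analysable.

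It would go too far to say that the analysis cannot show any relation between cortisol and change. Power of 24% is poor but not nil, and a level does carry some information about change. The accurate statement is that, read literally, the model tests the objective only indirectly and inefficiently, with a sign that depends on an unstated choice. This should be corrected.

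**What to change.** - **Relaxation.** Model the continuous pre-to-post change in relaxation on the change in cortisol over the same session, allowing for repeated sessions per person, with arm and centre in the model. Report the within-arm slope with its 95% CI.
- **PWB.** First reconcile Trial Design with Table 1 on whether cortisol was sampled at baseline. If it was, fit the corresponding model for change from baseline to T4. If it was not, state that a matching-interval analysis is not available for PWB.
- **Ordinal version.** If it is kept, call the groups tertiles and make it secondary or descriptive.
- **Optional.** Log transformation of cortisol, and separating within-person from between-person effects.

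**Cost.** For relaxation, only wording: the session data are already scheduled. For PWB, the cost cannot be assumed to be nil, because data collection ended on October 31, 2025 and a baseline sample that was not taken cannot be added. Analysis was expected to conclude in April 2026, so the rule should be fixed and dated before the objective 4 results are seen. If they have already been seen, the revised model should be reported as post hoc.

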**Objective:**

This study aims to assess the efficacy of Chinese art activities or their combination with peer group participation in enhancing PWB among Chinese older adults living in a residential center.

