### Conceptual Framework

The study is based on aesthetic theory and social support theory. Aesthetic theory underscores the significance of aesthetic experience in enhancing well-being via emotional and sensory reactions to art [32,33]. Interaction with beauty is correlated with favorable emotional states, which neuroscience links to the release of neurotransmitters such as endorphins and serotonin as well as a decrease in stress-related indicators, including cortisol [34-37]. Social support theory emphasizes that interpersonal interactions mitigate stress and improve well-being by providing emotional, informational, and companionship support [38-42]. Aesthetic theory corresponds to the creative process of Chinese painting and calligraphy in the Chinese art activity component of this intervention, mainly supporting the mechanisms of changes in emotional states and self-esteem levels. Social support theory corresponds to the peer group participation component, mainly guiding the mechanism of changes in perceived social support and loneliness. The concept structure of this study is shown in Figure 1.

This study is an exploratory trial. PWB, happiness, relaxation, loneliness, and salivary cortisol levels were selected as the dependent variables. Happiness, relaxation, and loneliness are all operationally defined as an immediate, subjective, and transient affective state characterized by momentary feelings [43,44]. Usually, PWB requires intervention for a longer period to manifest changes. However, as an exploratory trial, we still included it as an exploratory outcome measure to provide preliminary data for future research.

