**Figure 2. F2:**
[figure not shown]
The implementation phase and data collection procedures.

Outcome measures are gathered 30 minutes prior to and following each intervention session to assess immediate effects. A concluding follow-up assessment takes place 1 week after the final session to examine enduring outcomes. Figure 3 illustrates the research design within a single environment. The study protocol (version 1.0 dated March 2, 2026) complies with the SPIRIT (Standard Protocol Items: Recommendations for Interventional Trials) checklist (Table 1).

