### Outcomes

This research uses a repeated-measure design. In addition to the measurements obtained concurrently with the PWB assessment at baseline and 1 week after the intervention, further pre- and postintervention evaluations are performed for the happiness, relaxation, and loneliness scores and salivary cortisol levels. The schedule of evaluations is outlined in Table 1.

Demographic variables include age, gender, marital status, number of children, educational level, number of chronic diseases, type of residence (private or shared room), length of stay in the older adult center, frequency of monthly visits, and MMSE score.

The PWB score is assessed using the 18-item Chinese version of the PWB scale by Ryff [63]. This scale consists of 18 questions with 3 questions per dimension, covering a total of 6 dimensions: self-acceptance, positive relations with others, autonomy, environmental mastery, purpose in life, and personal growth.

The happiness, relaxation, and loneliness scores are measured using a specific 10-cm visual analog scale (VAS) [64-67]. After a decision is made, the recorded value is measured in millimeters (from left to right) using a ruler to assign a numerical value to the subjective evaluation, with possible scores ranging from 0 to 10. An example of the VAS is shown in Figure 4.

The VAS is a widely recognized and proven effective evaluation tool for subjective experience measurement in the older adult population [64,68-72]. However, studies have also shown that patients with cognitive decline, decreased hand flexibility, and impaired vision may find it difficult to complete, leading to unreliable results [71,73,74]. Therefore, the inclusion criteria stipulated requirements for MMSE scores higher than 24 and the ability to independently read and write. At the same time, the scale uses clearly marked and high-contrast black lines to ensure visual clarity, and during the first use, researchers will explain and demonstrate how to complete the scale to ensure that effective results are obtained from the participants.

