### Statistical Methods

This study will use computer-based data analysis with the following statistical procedures.

After data collection is completed, the RA will review and remove any missing data. Before inputting the results into the computer to create a dataset, all data need to be checked, and errors need to be corrected. Descriptive statistics will be used to analyze and describe the demographic data of the participants.

In this study, the dependent variables are PWB, happiness, loneliness, relaxation, and salivary cortisol levels, and the independent variables are interventions (Chinese art activities, Chinese art activities+peer group participation, and routine care). Descriptive statistics will be used to check for missing values, out-of-range data, and data accuracy. Histograms, skewness, and kurtosis will be used to test the normality of the dependent variables in each group. If the data follow a normal distribution, the mean and SD will be used for analysis. If they are not normally distributed, the median and IQR will be used to represent them.

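### The tests assigned to objectives 1 to 3 omit PWB, so the stated plan has no arm comparison on the outcome its objective names; no analysis names the 1-week follow-up

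*Protocol article*

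**What the plan says.** **What the trial is for.** The abstract's only stated objective is to "assess the efficacy of Chinese art activities or their combination with peer group participation in enhancing PWB among Chinese older adults". In the Objectives section, objective 1 asks whether "new residents in Chinese older adult centers have higher PWB scores, happiness, and relaxation" after the art activities. Objective 2 asks the same for the combined intervention, and objective 3 compares the two active arms. PWB comes first in all three, and the first hypothesis expects both interventions to raise it.

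**Its status.** Conceptual Framework calls the trial exploratory and notes that PWB usually needs a longer intervention to change. It adds that "we still included it as an exploratory outcome measure to provide preliminary data for future research".

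**When it is measured.** Outcomes refers to "the measurements obtained concurrently with the PWB assessment at baseline and 1 week after the intervention", and Table 1 shows PWB at enrolment and T4 only. Trial Design gives the purpose of T4: "A concluding follow-up assessment takes place 1 week after the final session to examine enduring outcomes". Table 1 has all five outcomes collected then.

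**How it is analysed.** Statistical Methods first states that "the dependent variables are PWB, happiness, loneliness, relaxation, and salivary cortisol levels", with intervention as the independent variable. It then goes objective by objective. The paired t tests for objectives 1 and 2 address effects "on happiness, relaxation, loneliness, and salivary cortisol levels before and after the intervention (3 times"). The independent-sample t tests against control, and the one for objective 3, repeat the same four outcomes. Objective 4 relates cortisol to categorised change in PWB or relaxation by ordered logistic regression. The paragraph ends: "There will be no additional analyses".

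**The concern.** A plan that lists the outcomes for each test and then closes the list can be read literally. Read that way, it never compares the arms on the outcome in the trial's objective. The objective 4 model cannot fill the gap. It asks whether cortisol tracks change in PWB and has no stated term for treatment, so it says nothing about whether either intervention raises PWB.

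The Conclusions, in the abstract and at the end of the article, look to evidence on enhancing PWB, and Anticipated Findings expects to identify the better programme. For PWB, the listed tests support neither. The investigators would have to leave the objective unanswered or report a PWB comparison outside their own plan, which a reader could fairly treat as chosen after the fact.

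A lesser gap concerns the follow-up. It is collected to look at lasting effects, but no analysis is tied to it by name.

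**Working it through.** The plan gives no PWB figure to reproduce, so the check sets its statements side by side.

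| Analysis in Statistical Methods | Outcomes listed | PWB? | Time point stated |
|---|---|---|---|
| Objectives 1 and 2, paired t tests within arms A and B | happiness, relaxation, loneliness, cortisol | no | pre/post at the 3 sessions |
| Objectives 1 and 2, independent t tests vs control | same four | no | none |
| Objective 3, independent t test, B vs A | same four | no | none |
| Objective 4, ordered logistic regression on cortisol | change in PWB; change in relaxation | yes, no treatment term stated | none |

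**PWB.** Applying the plan's own pairings to PWB gives 3 arm comparisons: A vs C, B vs C and B vs A. The number specified is 0. Dependent variables with a between-group test: 5 − 1 = 4 of 5.

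**T4.** Analyses that name the 1-week follow-up: 0. T4 data are still used in one place. PWB is measured only at enrolment and T4, so the change in PWB under objective 4 must be the difference between those two measurements.

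**What an added PWB comparison could show.** The documents give no PWB effect size; the sample size rests on loneliness (d = 0.92). For two arms, two-sided α = .05 and 80% power, the detectable difference is approximately d = (1.96 + 0.84) × √(2/n).
- 30 per arm: 2.80 × √(2/30) = 0.72; the exact t-test calculation gives 0.74.
- 24 per arm (30 less 20% dropout): 2.80 × √(2/24) = 0.81; exact 0.83.

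Power over an assumed range of true PWB effects (exact t test):

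| Assumed d | 30 per arm | 24 per arm |
|---|---|---|
| 0.2 | 12% | 10% |
| 0.3 | 21% | 17% |
| 0.5 | 48% | 40% |
| 0.8 | 86% | 77% |

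These figures are unadjusted for baseline. They support reporting PWB as an exploratory estimate with an interval; they are not a reason to leave the comparison out.

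**The case against.** **PWB is only exploratory, and the sample size rests on loneliness, which is tested.** This is true and bears on how the result is presented. It does not supply an analysis. Preliminary data for later research would need at least an estimated arm difference. Statistical Methods does imply descriptive PWB summaries by group, but these are not a comparison.

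**Detail may sit in a fuller plan.** That would excuse silence. Here the article names the outcomes test by test and then closes the list, so a fuller plan that compared arms on PWB would contradict this text.

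**The closing sentence may mean only no subgroup, sensitivity or adjusted analyses.** That reading is possible. Since PWB is listed as a dependent variable of intervention, and objectives 1 and 2 are promised both intra- and intergroup comparison, an accidental omission is more plausible than a deliberate ban. Even on the narrow reading, no PWB test is specified.

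**The follow-up.** Here the objection largely succeeds against a stronger reading. A reader might infer that T4 is never analysed, or count 36 between-arm session tests (4 outcomes × 3 pairs × 3 sessions) against 0 of 15 at T4 (5 outcomes × 3 pairs). The document does not support this. The restriction to three occasions stands only in the paired-test sentence, the between-group sentences name no time point, and objective 4 must draw on T4 PWB. Those counts carry a time restriction from one sentence into others that lack it.

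**Conclusion.** The PWB point holds: PWB is in objectives 1 to 3 and in none of their tests, so 0 of 3 arm comparisons on it are specified. This rests on reading the outcome lists as complete, which the closing sentence invites. The T4 point holds in a weaker form: no analysis names the follow-up, and for the other four outcomes it is unassigned rather than excluded. The exploratory label limits how strongly a PWB result could be stated, but it does not remove the mismatch between the objective and the analysis. Correction is worthwhile because the data exist and the trial otherwise does not answer its own question.

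**What to change.** 1. Add PWB to the analyses for objectives 1 to 3: A vs C, B vs C and B vs A at T4, with 95% confidence intervals, labelled exploratory in line with Conceptual Framework. The smallest repair is to add PWB to the existing t test lists. A comparison adjusted for baseline PWB, centre and the two minimisation factors (age band and visit frequency) is preferable, because it uses the baseline measurement and reflects how participants were allocated.
2. State the time points of the between-group tests for happiness, relaxation, loneliness and cortisol, including what is done at T4.
3. Reword the closing sentence so that the list it closes contains these analyses.
4. Record the change as a dated amendment and submit it to the institutional review board, as Ethical Considerations requires for any modification, before allocation codes are released to the analyst. Time is short: data collection ended on October 31, 2025, the protocol version is dated March 2, 2026, and analysis is expected to conclude in April 2026. If allocation is already known to those choosing the analysis, report these comparisons as post hoc.

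The cost is an amendment submission and a few more comparisons, to be reported as exploratory estimates. No further data collection is needed.
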